### 2.2. Participant Eligibility and Consent

All consecutive patients will be considered candidates for inclusion in the study if they meet all inclusion criteria and none of the exclusion criteria (Figure 2.). Eligible patients will receive oral and written information and will be enrolled after giving written informed consent.

**Inclusion criteria.** Inclusion criteria will be: (i) over 18 years of age, (ii) affiliated to or beneficiary of a social security scheme, (iii) informed consent signed after clear and fair information about the study, (iv) patient having signed a GPs declaration with the investigating physician, (v) indication for investigation and treatment of Hp infection according to HAS recommendations (suffering from chronic dyspepsia, iron deficiency anemia with no known cause or resistant to iron supplementation, vitamin B12 deficiency with no known cause, family history of gastric cancer, immunologic thrombocytopenic purpura in adulthood, personal history of peptic ulcers or pre-cancerous lesions that have not been eradicated, long-term use of NSAIDs or PPI, patient who received Hp eradication therapy without eradication control, patient with a predisposition syndrome for digestive cancers (hereditary non-polyposis colorectal carcinoma cancer)), (vi) patient with partial gastrectomy or endoscopic treatment of gastric cancer, (vii) patient with gastric pre-neoplastic lesions (severe atrophy and/or intestinal metaplasia, dysplasia), and (viii) patient with previous endoscopy for Hp without antibiotic susceptibility testing (biopsy not referred to bacteriology) and for whom guided therapy is requested.

**Non-inclusion criteria.** Patients who will not be included are those who: (i) are legally protected; (ii) are pregnant or breastfeeding women or women of childbearing age without effective contraception; (iii) are suspected of or have a documented allergy to amoxicillin; (iv) have a contraindication to (or initial refusal of) esophageal endoscopy; and (v) have an indication for upper GI endoscopy in the emergency department according to the criteria of the European Panel on the Appropriateness of Gastrointestinal Endoscopy (i.e., upper GI bleeding, acute deglobulation without externalized GI bleeding, caustic ingestion, acute dysphagia or foreign body ingestion).

### 2.3. Study Outcomes

**Primary endpoint.** The primary endpoint will be an assessment of the cure rate through the results of a urea breath test performed 6 weeks after the end of treatment (proof of Hp eradication).

**Secondary endpoints.** The secondary endpoints will be assessment of: (i) the number of guided treatments (depending on the real-life application of the French authorities recommendations); (ii) the number of endoscopies (estimating the number of endoscopies avoided due to the optimized process); (iii) the number of biopsies at endoscopy; (iv) the number of patients who refused endoscopy after serology or positive PCR or did not follow-up after referral to the gastroenterologist; (v) the number of treatment side-effects and treatment dropouts; (vi) the discordance rate between real-time PCR tests in stool and serology in primary diagnosis; (vii) the discordance rate between real-time PCR tests in stool/breathing test in eradication control; and (viii) cure rate assessed by the result of a urea breath test performed 6 weeks after the end of treatment (proof of Hp eradication) depending on the antibiotic susceptibility testing identified at diagnostic.

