The main objective of this study will be to evaluate, in a real-life situation, the feasibility of a strategy for the management of Hp infection by a non-invasive procedure in primary care and its non-inferiority in eradication rate compared with the strategy recommended by the HAS using a combination of serology and endoscopy. The secondary objectives of this study will be: to evaluate the adherence of patients to the care pathway (compliance to endoscopy, treatment, stool collection, serology); to evaluate the follow-up of recommendations in the management of Hp infections by health professionals (GPs and gastroenterologists) (e.g., empirical/guided treatment, evaluation of pre-neoplastic lesions); to validate, in real-life circumstances, real-time PCR in stool in comparison with serology in primary diagnosis and with urea breath test in eradication control.

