
**Control group.** Patients randomized to the reference strategy control group (HAS strategy arm) will receive a prescription for Hp serology and a stool self-sampling kit (instructions, biodegradable basket to be placed on the toilet seat, E-Nat tube (Copan), swab, stamped envelope for mailing to the laboratory). Only the serology result will be considered for this arm (to avoid any deviation from the protocol, results of other tests will not be communicated before the end of the study). According to the results of their biological assay, patients will be seen by their investigator within six weeks. A positive serological test will lead to a gastroscopy with biopsies for histology/pathological and bacteriological analysis if available. Each person referred will be accompanied by the “request for gastroscopy in case of positive Hp serology” letter, according to the HAS model. These anatomopathological and/or bacteriological analyses will determine the presence of a Hp infection, if bacteria suggestive of Hp are observed in pathological examination and/or if the conventional and/or molecular biology are positive from gastric biopsies sent to bacteriology laboratories. An infection will determine the indication for treatment, either empirically, in the absence of an antibiogram or PCR result (bismuth or concomitant quadritherapy), or guided by the results of the AST or culture according to HAS recommendations (pertinence of care sheet). At least 4 weeks after stopping antibiotics (and at least 2 weeks after stopping PPIs), an eradication control will be carried out using a respiratory test (urea breath test), concomitant to collection of a stool sample for retrospective analysis by PCR. A negative breath test will define the success of the treatment, while a positive test will define treatment failure. The latter will be managed in the usual manner by the GPs in charge of the patient.

It should be noted that for ethical and regulatory considerations, it was decided, after the collection of results (at the end of the study for each patient), to give out the results of these analyses (urea breath test, serology, PCR before/after treatment) in order to allow the general practitioner to manage the patient in an appropriate manner.

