### 2.5. Statistical Analysis

**Sample size calculation.** Assuming 20% prevalence in source population, and based on a one-sided hypothesis, 100 patients will be included in each strategy arm to demonstrate a 15% difference between each strategy with statistical risks at 5% (type I error, α) and 15% (type II error, β). We are planning to enroll 1000 patients to consider a maximum patient loss of 10%. Considering that each investigator involved in the HepyPrim study follows more than 1200 patients each year, the inclusion objective was set to 50 patients per investigator and the number of investigators was set to 20. These investigators have been selected in the newly constituted “physicians’ network for research in New Aquitaine”.

**Analysis.** The data will be analyzed blindly on an intention-to-treat basis, assuming a non-inferiority hypothesis. No interim analysis is planned. A per protocol analysis will be performed as a secondary sensitivity analysis. Quantitative variables will be described by their mean and standard deviation or median and interquartile range according to the normality of the distribution. Categorical variables will be described by their number and percentage. Continuous variables will be compared by a Student’s *t*-test or Mann–Whitney U-test according to the normality of the distribution. Categorical variables will be compared by a chi-square test or Fisher’s exact test. The tests will be analyzed using GraphPad Prism version 9.0 (GraphPad Software, San Diego, CA, USA). A significant difference will be retained for a *p*-value < 0.05. All tests will be two-tailed, stratified by center and for multiple comparisons if appropriate.

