Moreover, this is the first study to enable the structuring of a research network in primary care in Poitou-Charentes. This project is the first of this network, which will be made up of 20 co-investigators, all of whom are GPs. Others were identified during the recruitment phase carried out as part of a thesis on the practice of general medicine by two interns in general medicine. This project is therefore founding and structuring for a primary care research network.

This study may allow evaluation of the performance of PCR in stools in comparison with the combination of serology/pathology/bacteriology for the initial diagnosis, evaluation of the performance of PCR in stools in comparison to the respiratory test for the control of eradication. Moreover, it may lead to the constitution of a biobank of stools of infected patients, in view of further study of the development of in vitro diagnosis.

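### Secondary endpoint (vii) validates post-treatment stool PCR by a discordance rate, which pools missed failures with over-called cures; sensitivity and specificity against the breath test should be named instead

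*Protocol article*

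**What the plan says.** The Introduction of the protocol article sets, among the secondary objectives, "to validate, in real-life circumstances, real-time PCR in stool in comparison with serology in primary diagnosis and with urea breath test in eradication control". The Discussion describes the same aim as "evaluation of the performance of PCR in stools in comparison to the respiratory test for the control of eradication".

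Section 2.1 makes the breath test the arbiter of outcome in both arms: "A negative breath test will define the success of the treatment, while a positive test will define treatment failure". The post-treatment stool sample is paired with it; in the control arm the breath test is described as "concomitant to collection of a stool sample for retrospective analysis by PCR", and the intervention arm has the equivalent arrangement.

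The measure for this comparison is in section 2.3: "vii) the discordance rate between real-time PCR tests in stool/breathing test in eradication control". Sensitivity, specificity, positive or negative agreement and kappa are not named for eradication control. Section 2.5 adds only counts, percentages and chi-square or Fisher tests for categorical variables. Section 2.4 lists both the post-treatment PCR result and the breath-test result among the data recorded.

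**The concern.** The objective is a validation against a reference, and the measure does not match it. Once the breath test defines success and failure, a PCR can be wrong in two ways: it can be negative in a patient who is still infected, or positive in a patient who is cured. These errors have different consequences, and a discordance rate adds them together.

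Everyone who reaches eradication control has been treated. If most are cured, the rate is weighted towards breath-test negatives, and the few failures, which carry all the information on sensitivity, contribute little to it. A modest rate could then come from a test that misses many failures or from one that finds them all and over-calls some cures. A reader who wants to know whether stool PCR could stand in for the breath test needs to tell these apart.

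**Working it through.** **Inputs**

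- Reference: the breath test (section 2.1).
- Number of pairs: section 2.5 says "100 patients will be included in each strategy arm to demonstrate a 15% difference between each strategy". With the stated 20% prevalence and 1000 enrolled, 1000 × 0.20 = 200 infected patients, which fits 100 per arm. I take 200 pairs. After the stated 10% loss it would be 180.
- Cure rate c: not stated. Assumed range 80% to 95%.
- PCR performance: the Introduction quotes sensitivity 96.3% and specificity 98.7%, not stated for post-treatment use. Used only as a benchmark.

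**Step 1. The plan's own figure.** The 100 per arm cannot be reproduced without a cure rate, but it can be solved backwards. For non-inferiority with equal cure rates p, margin 0.15, one-sided 5% and power 85%:

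n per arm = (1.645 + 1.036)² × 2p(1 − p) / 0.15²

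This gives 120 at p = 0.75, 103 at 0.80, 99 at 0.81 and 82 at 0.85. The closest match is a cure rate of about 80%. Other readings of the calculation (one-sided 2.5%, or superiority) put it roughly between 75% and 90%. This supports the assumption that most patients are cured, but it is an inference.

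**Step 2. What the rate shows.** With the breath test as reference:

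discordance = (1 − c)(1 − sensitivity) + c(1 − specificity)

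| Assumed cure rate | Failures in 200 | PCR always negative | Misses half, specificity 100% | Quoted 96.3% / 98.7% |
|---|---|---|---|---|
| 80% | 40 | 20% | 10% | 1.8% |
| 85% | 30 | 15% | 7.5% | 1.7% |
| 90% | 20 | 10% | 5% | 1.5% |
| 95% | 10 | 5% | 2.5% | 1.4% |

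**Step 3. Same rate, opposite tests.** At 90% cure there are 20 failures and 180 cures.

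- Test A misses 10 of 20 failures and makes no other error: 10/200 = 5.0% (sensitivity 50%, specificity 100%).
- Test B finds all 20 failures and calls 10 of 180 cures positive: 10/200 = 5.0% (sensitivity 100%, specificity 170/180 = 94.4%).

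Similarly, a test blind to every failure gives 20/200 = 10.0% (exact 95% CI 6.2% to 15.0%). One that finds every failure with 90% specificity gives 18/200 = 9.0% (5.4% to 13.9%).

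**Step 4. When the rate is informative.** With D discordant pairs and F failures, at most D failures were missed, so observed sensitivity is at least 1 − D/F. With D = 4 and F = 40, at least 36/40 = 90% were detected. With D = 10 and F = 20, sensitivity lies anywhere from 10/20 = 50% to 100%.

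**Step 5. What the split would give.** Exact 95% CIs for sensitivity:

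| Assumed cure rate | Failures | Detected | 95% CI |
|---|---|---|---|
| 80% | 40 | 36 (90%) | 76% to 97% |
| 90% | 20 | 18 (90%) | 68% to 99% |
| 95% | 10 | 9 (90%) | 56% to 99.7% |

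With 180 pairs the failures fall to 36, 18 and 9.

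**The case against.** The strongest reply is that the pooling is read into the text. Section 2.3 does not say that the two discordant cells will be merged or that the 2×2 table will be withheld. The Discussion speaks of the performance of PCR, and the Introduction uses that word for sensitivity and specificity. How an agreement endpoint is tabulated is commonly left to an analysis plan, which is not shown, and the recorded data allow the split. This stands to the extent that nobody can say the split will not be reported. It does not remove the point: the protocol names a measure, that measure is a rate of disagreement, and the Discussion sentence names no statistic.

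A reader might infer three stronger things that the documents do not support.

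- *That the endpoint cannot answer the validation question at all.* Step 4 shows otherwise: a very low rate, set beside the number of breath-test failures known from the primary endpoint, bounds sensitivity from below. At 80% cure, a test that misses half of the failures would show 10%, well above the 1.8% implied by the quoted performance.
- *That a poor PCR would be declared validated.* No discordance threshold or decision rule is stated, so this is conjecture.
- *That validation must rest on sensitivity alone.* The documents do not rank the two errors. Doing so is a preference.

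**Conclusion.** The point holds as a mismatch between a validation objective and the measure named for it. Taken alone, the discordance rate does not separate missed failures from over-called cures. At assumed cure rates of 80% to 95%, a PCR that misses half of the failures would show 10% to 2.5% discordance, and at 90% cure two opposite tests share the same 5%. The pooling is a weakness at any cure rate; a high cure rate makes it worse. The sizes rest on an unstated cure rate and on 200 paired results.

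The importance is minor. Post-treatment PCR is analysed retrospectively and does not define treatment success, so the primary endpoint and the non-inferiority comparison are untouched.

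**What to change.** Reword (vii) as two quantities: sensitivity (positive agreement) of stool PCR among breath-test positives, and specificity (negative agreement) among breath-test negatives. Give each with its denominator and an exact 95% CI. Keep the overall discordance rate as a descriptive figure.

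No extra sample, visit or patient is needed, because the same 2×2 table supplies everything. The cost is that the sensitivity interval will be openly wide, with about 10 to 40 failures behind it if 200 patients are tested and cure is 80% to 95%. That imprecision is there already; the single rate only hides it.

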### 2.4. Data Collection

Independent clinical research assistants will be available at each participating hospital to help in running the study and with data collection. Study documents will be deidentified and stored for 15 years, as per the protocol for non-clinical trial notification interventional studies. Data will be entered into the web-based eCRF (https://chu-poitiers.hugo-online.fr/CSOnline/, accessed on 27 December 2021) and electronically stored on double password-protected computers. Hard copies of data (clinical research files) will be stored in a secure locked office. All personnel involved in data analysis will be masked to study groups. Only the principal investigators and the statisticians will have access to the final data set.

The following data will be recorded:

**Baseline characteristics.** (i) Demographic data (age, gender, height, weight, and body mass index); (ii) comorbidities (active smoking, insulin-dependent or non-insulin-dependent diabetes, hypertension, hypercholesterolemia, chronic renal failure, COPD); (iii) history of antimicrobial treatment for eradication of *H. pylori*; (iv) key laboratory findings (except for Hp); (v) familial history of cancer; and (vi) symptomatology (including clinical examination).

**Biological data.** Results of the following biological assays: (i) Results of the stool PCR searching for *H. pylori* (before and after eradication treatment); (ii) serological status of the patient regarding *H. pylori*; (iii) histopathological results (for HAS groups); and (iv) results of the urea breath test.

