## 2. Methods

### 2.1. Trial Design and Setting 

This study will be a prospective, multicenter, randomized, controlled interventional study in two arms (Figure 1). Randomization will be carried out through a secure web-based randomization system and stratified by center (i.e., each investigator). The duration of the inclusion period will be 12 months. The participation period for each participant will be 4 months for a total study duration of 16 months (twelve months of inclusion plus four months of follow-up for the last included patient).

A computer-generated block-randomization sequence using permuted-block randomization of varying block sizes will be performed by the statistician and will be carried out via Ennov System software. The statistician will not be involved in either screening the patients or assessing outcomes. The randomization process will be accessible to all physicians working in the emergency department through user personal identification logins to access the website (https://chu-poitiers.hugo-online.fr/CSOnline/, accessed on 27 December 2021). It will become effective following confirmation of inclusion and exclusion criteria. Thereafter, patients will be assigned to one of the two study groups (in a 1:1 randomization scheme) according to the strategy (described thereafter).

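### The stated comparison of cure rates uses center only and leaves out previous eradication treatment, a recorded and plausibly prognostic baseline variable; adjusting for it is a modest, cheap gain in efficiency

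*Protocol article*

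**What the plan says.** - **Endpoint.** Section 2.3 defines the primary endpoint as an "assessment of the cure rate through the results of a urea breath test performed 6 weeks after the end of treatment", a yes/no outcome per patient.
- **Eligibility.** Section 2.2 lists among the qualifying indications a "patient who received Hp eradication therapy without eradication control". Previously treated and untreated patients therefore enter the same comparison.
- **Baseline data.** Section 2.4 records "history of antimicrobial treatment for eradication of" H. pylori. The variable is known before treatment and needs no extra procedure.
- **Test.** Section 2.5 states: "Categorical variables will be compared by a chi-square test or Fisher’s exact test". It adds: "All tests will be two-tailed, stratified by center and for multiple comparisons if appropriate". Center is the only factor named.
- **Randomization.** Section 2.1 allocates patients "in a 1:1 randomization scheme", with center, meaning the individual investigator, as the only stratification factor.
- **Sample size.** Section 2.5 rests on 100 patients per arm, a 15-point difference, one-sided alpha of 5% and beta of 15%. It states no expected cure rate.

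**The concern.** The Introduction names resistance to the antibiotics used as the leading reason that eradication fails, with poor compliance second. A patient who has already taken such antibiotics and is found infected is plausibly more likely to carry a resistant strain, and so less likely to be cured. If so, treatment history explains part of the variation in outcome, and a test that uses only center leaves that part in the standard error.

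The non-inferiority decision rests on about 100 infected patients per arm, or about 5 per arm at each of 20 investigators. At that size a narrower interval around the cure-rate difference is worth having if it costs almost nothing. The choice has to be made in advance, because an adjustment added after the data are seen would be open to challenge.

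**Working it through.** **Inputs from the protocol article, section 2.5:** n = 100 per arm; 15 points, read as the non-inferiority margin; one-sided alpha 5% (z = 1.645); power 85% (z = 1.036).

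**Assumptions, not in the document:** cure rate p = 0.80 in both arms; share previously treated f = 5% to 40%; cure rate lower by d = 10 to 30 points in those patients. The middle case is f = 20%, d = 20 points, which means 84% cure in untreated and 64% in previously treated patients.

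**1. The plan's own figure.** n per arm = (1.645 + 1.036)² × 2p(1−p) / 0.15².
- p = 0.80: 103
- p = 0.81: 99
- p = 0.75: 120
- p = 0.85: 82

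The stated 100 fits a cure rate near 80%. It cannot be confirmed, because no rate is given. This is why 80% is used below.

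**2. Power without adjustment.** SE = √(2 × 0.80 × 0.20 / 100) = 0.0566. Power = Φ(0.15/0.0566 − 1.645) = Φ(1.007) = 84.3%.

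**3. Variance explained by previous treatment.** R² = f(1−f)d² / [p(1−p)]. In the middle case this is 0.20 × 0.80 × 0.04 / 0.16 = 0.04. As a check, the average within-group variance is 0.20 × 0.64 × 0.36 + 0.80 × 0.84 × 0.16 = 0.1536, which is 0.96 × 0.16.

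**4. Power with adjustment.** The SE is multiplied by √(1−R²).

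| f | d (points) | R² | Power at 100 per arm |
|---|---|---|---|
| 5% | 10 | 0.3% | 84.4% |
| 10% | 10 | 0.6% | 84.5% |
| 20% | 20 | 4.0% | 85.6% |
| 30% | 30 | 11.8% | 88.1% |
| 40% | 30 | 13.5% | 88.6% |

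In the middle case the required n falls from 103 to 103 × 0.96, or 99 per arm.

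**5. Chance imbalance.** The SD of the between-arm difference in the share previously treated is √(2f(1−f)/100). In the middle case it is 5.7 points. Multiplied by d = 0.20, one SD moves the crude cure-rate difference by 1.1 points. This is not a second loss: SE × √R² = 5.66 × 0.20 = 1.1 points, so it is the same 4% of variance in another form.

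**6. Can the model carry center?** At 80% cure, 200 infected patients give about 40 failures, or 2 per investigator. A logistic model with 20 center terms, arm and previous treatment has about 22 parameters, so about 40/22 = 1.8 failures per parameter. That is too few for fixed center effects.

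**The case against.** **The comparison is already valid, and this is preference.** The first half stands. Randomization protects the unadjusted comparison, and its standard error already allows for chance imbalance. A reader might infer that an imbalance in previous treatment would bias the result, or that imbalance is a harm on top of lost precision. The documents support neither, and step 5 of the working shows that the two are one quantity.

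**The plan does account for center.** This stands. It would be wrong to say that the analysis uses no stratification or covariate at all; what is absent is anything beyond center.

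**The prognostic effect is assumed.** This also stands. The Introduction blames resistance and compliance and does not mention previous treatment. No cure rate by history and no share previously treated is given. Section 2.1 lets treatment be guided by detected resistance, which could narrow the gap. The top of the range needs 92% cure in untreated and 62% in previously treated patients, and nothing in the document points to that.

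**Covariates belong in the full protocol or analysis plan.** This stands in part. Neither is shown, and either may already name covariates, so the point concerns the analysis the article states. That analysis does name a test and a stratification factor, so it can be improved as written.

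**Adjustment is not free with sparse centers.** This is correct for fixed center effects. It governs how center should be handled and does not defeat adjustment for one yes/no variable.

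**Conclusion.** The point holds as a modest efficiency improvement. The stated test uses center only, while a variable that plausibly predicts cure is already collected. In the middle case adjustment adds 1.3 points of power (84.3% to 85.6%). The gain is close to nothing if few patients were treated before, and about 4 points only if many were and their cure rate is far lower. All of this rests on the assumed 80% cure rate, the assumed share and gap, and 100 evaluable infected patients per arm.

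A reader might go further and conclude that the primary analysis is wrong or its result untrustworthy. The document does not support that: the unadjusted comparison is sound, and previous treatment as a predictor is an inference from what is said about resistance. Adjusting for this one factor would also not remove other differences that could arise because the two arms identify infection by different routes.

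**What to change.** In section 2.5, or in the analysis plan, prespecify the following:

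- **Primary estimate.** The marginal difference in cure rate between arms with its confidence interval, compared with the 15-point margin and adjusted for previous eradication treatment (yes/no). Logistic regression with standardization is one suitable method, and it keeps the result on the absolute scale of the margin.
- **Center.** A random effect, or pooling of small centers, in place of 20 fixed effects.
- **Fallback.** A simpler named analysis if the model does not converge.
- **Supportive analysis.** The center-stratified unadjusted difference.

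The cost is wording and slightly more analysis work. The variable is already recorded, and no additional patients, visits or procedures are needed.
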